#### Patient-related secondary endpoints

Change in patient-rated depressive symptoms (BDI-II total score) and therapy dropout at the remaining measuring times.

Relating to the difference from baseline to 20 and 35 weeks, 20 and 36 months after baseline:

Observer-rated depressive symptoms (Hamilton Rating Scale for Depression,^81 82^ total score of the 21-item version). Excellent inter-rater reliability (ICC, intraclass correlation coefficient=0.95), Cronbach’s α: 0.78.Patient-rated anxiety (Generalised Anxiety Disorder Scale-7,^83^ total score, rated on a 4-point Likert scale, 0 ‘not at all’ to 3 ‘nearly every day’). Cronbach’s α: 0.92, good test–retest reliability (ICC=0.83).^83^Patient-rated somatic symptoms (Patient Health Questionnaire-15,^84^ total score, ratings of problems in the last 4 weeks, 0=‘not bothered at all’ to 2 ‘very bothered’). Cronbach’s α: 0.80; validity was proven.^85^Patient-rated personality structure deficits (Operationalised Psychodynamic Diagnosis-Structure Questionnaire, short version,^86^ total score, 12 items assessing personality functioning, rated on a 4-point Likert scale, 0 ‘does not apply at all’ to 4 ‘does apply completely’). Cronbach’s α: 0.89.^86^Patient-rated interpersonal problems (Inventory of Interpersonal Problems-Revised, IIP-32,^87^ total score, 32 items scored on a 5-point Likert scale). Adequate internal consistency was demonstrated. Cronbach’s α of the subscales: 0.68–0.90.^88^Patient-rated quality of life (WHO Quality of Life, short version, WHOQOL–BREF,^89^ 5-point Likert scale, 1 ‘not at all’ to 5 ‘completely/to an extreme amount’). We will use two dimensions: physical and psychological quality of life. Cronbach’s α of the subscales: 0.57–0.88.

#### Therapist-related secondary endpoints

Difference in observer-rated interpersonal skills from baseline to week 35 after baseline of the first patient (Facilitative Interpersonal Skills (FIS) Performance Test, FIS,^90^,^93^ total score, eight items measuring general interpersonal skills based on verbal responses to six video clips displaying challenging therapy situations—verbal fluency; hope; persuasiveness; emotional expression; warmth, acceptance and understanding; empathy; alliance bond capacity and rupture-repair responsiveness), 1 ‘low level’ to 5 ‘high level’ of skills). The German FIS version shows good inter-rater reliability (total score ICC=0.81). Cronbach’α: 0.95–0.96.^75 91^Therapist-rated retrospective satisfaction with supervision at week 20, 35, months 20, 36 after baseline of the first patient (modified version of the Client Satisfaction Questionnaire-8,^94^ total score, measuring satisfaction with supervision instead of treatment, CSQ-8-mod).^40^ Cronbach’α: 0.87–0.93, good concurrent validity for the total score.^95^

Relating to difference from baseline to 20 and 35 weeks, 20 and 36 months after baseline (all therapist rated):

Trait-like relational manner and therapeutic competence score (relational manner—trait section (35 items) and skills change index section (10 items) of the Adapted Trainee Current Practice Report which is originally used in the SPRISTAD trial and currently undergoing psychometric evaluation^96^).Emotional suppression (Emotional Regulation Questionnaire subscale score,^97^ 4 items, 1 ‘totally disagree’ to 7 ‘totally agree’). Cronbach’s α suppression subscale: 0.74.Alexithymia (Toronto Alexithymia Scale,^98^ total score and the difficulties (a) identifying and (b) describing feelings subscales, 5-point Likert scale, 1 ‘does not apply at all or not true at all’ to 5 ‘completely true’). Cronbach’s α: 0.80–0.86.^98^

#### Variables to assess potential mediators for M-AFT-D effectiveness

Average level of therapeutic alliance across sessions (German short revised version of the Working Alliance Inventory, WAI-SR,^99^,^101^ assessed after each session, 12 items). Cronbach’s α for the total score: >0.90. Convergent validity is established.^100^Convergence of patient’s and therapist’s alliance ratings over time (patient and therapist versions of the WAI-SR, total scores of session ratings; see above).Ratio of unresolved/resolved alliance ruptures (Post-Session-Questionnaire–modified version, PSQ-mod).^102 103^ The first item asks whether a ‘problem or tension’ occurred in the relationship between patient and therapist during the session. If answered with ‘yes’, the intensity of the rupture and the degree to which it could be solved is specified. Despite the simple nature of the items, there are clear indications of their validity.^102 103^Therapists’ usage of interventions referring to the therapeutic relationship in the here and now as well as usage of nondirective supportive techniques (mean of the categories ‘repeating, paraphrasing, summarising’, ‘expression of emotional sympathy’, ‘validation’); Psychodynamic Intervention List, PIL, observer-ratings based on transcribed therapy sessions on the level of verbal statements,^104^ 0 ‘category characteristics do not apply at all’ to 5 ‘category characteristics completely apply’. Satisfactory reliability and convergent validity; inter-rater reliabilities ICC ‘expression of emotional sympathy’ 0.69, ICC ‘validation’: 0.68, ICC ‘repeating, paraphrasing, summarising’: 0.80, ICC ‘referring to the therapeutic relationship’: 0.78, ICC topic ‘therapist’: 0.87.^56 104^Therapists’ empathy (Empathy Scale^105^), total score, 10-items, observer-ratings of video-taped sessions, 0 ’no agreement at all’ to 3 ‘very strong agreement’. Cronbach’s α: 0.86.^106^Therapists’ basic communication skills (Clinical Communication Skills Scale–short version;^107^ total score, 14 items, observer-ratings of video-taped sessions, 4-point scale ‘not at all appropriately’ to ‘entirely appropriately’). Reliability and validity were demonstrated.^107^Therapists’ adherence to AFT, CBT, PDT (BIFS^58^), observer-ratings of video-taped sessions, 12 items each (three subscales). Good psychometric properties, criterion validity and adequate inter-rater agreement have been demonstrated repeatedly.^108^

#### Variables for subsidiary research questions

Mediators of change (patient-rated, Mediators of change in Psychotherapy Inventory^109^), after each session, 22 items and 5 subscales: quality of the therapeutic relationship (7 items), patients’ perception and expression of feelings and thoughts (5 items), patients’ becoming conscious of biographical experiences (4 items), gaining a new view on problems (4 items) and patients’ self-disclosure (2 items). A five-factor structure with good psychometric properties could be found.^109^Parenting behaviour of therapist’s parents (German translation of the Measure of Parental Style Questionnaire, Fragebogen dysfunktionaler elterlicher Beziehungsstile,^110 111^ parenting style of father and mother, 15 items each, 1 ’does not apply at all’ to 4 ’does completely apply’). Cronbach’s α: 0.48–0.93.^111^Therapists’ personality traits (Big Five Inventory, short version,^112^ measuring extraversion, agreeableness, conscientiousness, emotional stability, openness, 10 items). Cronbach’s α: 0.49–0.62.^113^Therapists’ interpersonal problems (IIP-32, see patient outcomes).Therapists’ sensitivity to aversive interpersonal behaviour (Interpersonal Sensitivities Circumplex German Questionnaire,^114^ 40 items assessing the extent to which individuals are bothered by others’ interpersonal behaviours, 1 ’not at all, never’ to 8 ’extremely, always’). Cronbach’s α: 0.74–0.89.Therapists’ abilities to mentalise (Certainty About Mental States Questionnaire,^115^ 20 items, 0 ‘never’ to 1 ‘always’, measuring the perceived capacity to understand mental states of the self and others). McDonald’s Ω: 0.88–0.91, good validity and test–retest reliability.^115^Therapist’s dispositional fear of negative evaluation (Fear of Negative Evaluation Scale, FNE,^116^ German version–Skala Angst vor negativer Bewertung,^117^ 5 items, 1 ‘almost never applies’ to 4 ‘almost always true’). Cronbach’s α: 0.84–0.94.Therapists: Relational manner–state,^96^ 35 items, see therapist-related endpoints.Therapists’ perception of own competence and skills (FIS, self-rating; see therapist-related endpoints).Patients’ therapy expectations and therapy evaluation, PATHEV,^118^ 11 items, 1 ’not true at all’ to 5 ’completely true’, three subscales: improvement, fear of change, suitability. Cronbach’s α: 0.73–0.89.Patients’ early depressive symptom changes (pre to fifth session, BDI-II,^66 80^ see above).Distinctive internal reactions (Impact Message Inventory,^119^,^121^ observer-ratings, 64 items, 1 ’not true at all’ to 4 ’absolutely true’, dimensions: affiliation and dominance. Cronbach’s α: 0.84–0.89, inter-rater reliability, ICC: 0.30–0.58.Planned for the following funding period: Rupture Resolution Rating System,^122^ observer ratings, presence of a rupture and its clarity and intensity, 5-point Likert scale. Inter-rater reliability withdrawal rupture ICC: 0.85, confrontation ruptures ICC: 0.98.^123^Selected sessions will be analysed in terms of nonverbal behaviour and linguistic variables.(Note: It would have been valuable to video-record not only the therapy sessions but also the supervision sessions, as this could have provided deeper insights into adherence to MAFT-D and the rupture-repair processes occurring during supervision. However, due to the already highly complex study design, we decided not to include this component in the current study.

### Measurement time points

The data collection is summarised in table 1.

**Table 1 T1:** Data and measurement time points

Informant	Instrument	No. of items	Measurement points
Patient	BDI-II	21	Screening, BA, after the fifth therapy session, Post, FUP 1, 2, 3
	SCID-5-SPQ	106	Screening
	GAD-7	7	BA, Post, FUP 1, 2, 3
	PHQ-15	15	BA, Post, FUP 1, 2, 3
	OPD-SQS	12	BA, Post, FUP 1, 2, 3
	IIP-32	64	BA, Post, FUP 1, 2, 3
	WHOQOL-BREF	16	BA, Post, FUP 1, 2, 3
	PATHEV	11	BA
	Basic characteristics	app. 40	BA
	WAI-SR	12	After every session
	PSQ-Mod	3	After every session
	MOCPI	22	After every session
	Symptom severity VAS	1	After every session
	additional treatments	3	After every session
	INEP	21	Post, FUP 1, 2, 3
Observer interviews and ratings	SCID-5-CV	Adaptive	Screening
	SCID-5-PD	Adaptive	Screening or BA (depending on interview duration)
	adapted CSSRI	Adaptive	Screening, Post, FUP 1, 2, 3
	CSSR-S	23	Screening
	GRID-HAM-D-21	21	BA, Post, FUP 1, 2, 3
	Dropout-Interview	3	Flexibly
	BIFS-AFT	12	One session each of session 1-4/5-10, 11–16, 17–20 (if available)
	PIL	37	Sessions selected based on process data
	Empathy Scale	10	Sessions selected based on process data
	CCSS-S	14	Sessions selected based on process data
	IMI-R	64	Sessions selected based on process data
	3RS	22	Sessions selected based on process data
	FIS	6*9	BA, FUP1
Therapist	Basic characteristics, experience, practice	40	BA, Post, FUP 1, 2, 3
	Skills Change Index	10	BA, Post, FUP 1, 2, 3
	Relational Manner	35	BA, Post, FUP 1, 2, 3
	ERQ	10	BA, Post, FUP 1, 2, 3
	TAS-20	20	BA, Post, FUP 1, 2, 3
	FDEB	30	BA
	BFI-10	10	BA
	ISC-G	40	BA
	IIP-32	32	BA
	CAMSQ	20	BA
	SANB	5	BA
	FIS self-rating	9	BA, FUP 1
	CSQ-8-mod	8	Post, FUP 1, 2, 3
	WAI-SR	12	After every session
	PSQ-Mod	3	After every session
	Report on important events	Adaptive	flexibly
	Relational manner – state	35	After the fifth session
Supervisor	Basic characteristics, experience, practice	app. 10	BA
	Attendance sheet	4-5	After every supervision

BA, baseline assessment; BDI-II, Beck Depression Inventory–II^66 80^; BFI-10, Big Five Inventory–10^112^; BIFS, Beth Israel Fidelity Scale^58^; CAMSQ, Certainty about Mental States Questionnaire^115^; CCSS-S, Clinical Communication Skills Scale–short^107^; CSQ-8, Client Satisfaction Questionnaire-8, modified to supervision satisfaction^94^; CSSRI, Client Sociodemographic and Service Receipt Inventory^59^; CSSR-S, Colombia Suicide Severity Rating Scale^69^; ERQ, Emotion Regulation Questionnaire^97^; Empathy Scale^105^; FDEB, Fragebogen dysfunktionaler elterlicher Beziehungsstile^110^; FIS, Facilitative Interpersonal Skills^90^; FUP, follow up assessment; GAD-7, Generalised Anxiety Disorder Scale-7^83^; GRID-HAM-D, GRID Hamilton Rating Scale for Depression^81 82^; IIP-32, Inventory of Interpersonal Problems-32^87^; IMI-R, Impact Message Inventory^126^; INEP, Inventory for the assessment of Negative Effects of Psychotherapy^125^; ISC-G, Interpersonal Sensitivities Circumplex–German^114^; MOCPI, Mediators of Change in Psychotherapy Inventory^109^; OPD, operationalised psychodynamic diagnosis; OPD-SQS, OPD-Structure Questionnaire, short version^86^; PATHEV, Patientenfragebogen zur Therapieerwartung und Therapieevaluation^118^; PHQ-15, Patient Health Questionnaire-15^84^; PIL, Psychodynamic Interventions List^104^; Post, post-assessment; PSQ-Mod, Post-Session-Questionnaire, modified version^102 103^; Relational Manner–state and trait, and the Skills Change Index are both part of the Trainee Current Practice Report originally used in the SPRISTAD trial and currently under psychometric evaluation^127^; PSQ-Mod, Post-Session-Questionnaire, modified version^102 103^; 3RS, Rupture Resolution Rating System^123^; SANB, Skala Angst vor negativer Bewertung^128^; SCID-CV/PD, Structured Clinical Interview for DSM-5 Disorders, Clinician Version/ Personality Disorders^60 61^; TAS-20, Toronto Alexithymia Scale 20; VAS, Visual analogue scale^129^; WAI-SR, Working Alliance Inventory, short revised^100^; WHOQOL-BREF, WHO Quality of Life, short version^89^.

The number of items in the report on important events depends on which event (eg, study dropout, therapy dropout, hospitalisation) occurred. Important events should be reported as soon as possible, and the reporting is independent from scheduled sessions.

### Statistical analyses

Results are reported according to the Consolidated Standards of Reporting Trials (CONSORT) statement.^124^ Analyses are carried out with standard software: SPSS, V.29 or newer (IBM), SAS, V.9.4 or newer (SAS Institute), or R (V.4.3.3). A statistical analysis plan that contains the details of all planned analyses will be finalised before database lock.

Descriptive data are presented overall and separated by randomised group. As descriptive statistics, mean, SD, median, first and third quartile or minimum and maximum are calculated for continuous variables. For categorical variables, absolute and relative frequencies are reported.

First primary outcome (hypothesis I): We use a linear mixed model with repeated measures with changes from baseline as dependent variable, IG, therapeutic approach (CBT vs PDT), time and comorbid SCID5 personality disorder (yes vs no) as fixed effects, baseline BDI-II score as covariate, time by IG interaction, and cooperation centre, supervision group (if possible), therapist (=cluster) and patient as nested random effects. The interaction term is eliminated from the model if the corresponding interaction p value is >0.15. Measurement points up to and including the first follow-up (within the current funding period) will be considered. The contrast of the IG after 20 weeks is the result of the primary analysis. This result is considered in a confirmatory manner according to the approach described below. If the model fails to converge due to the complex cluster structure and variance components are estimated as zero, we will simplify the model stepwise by removing random effects.

Second primary outcome (hypothesis II): We perform a mixed logistic regression with the binary variable patient dropout after 20 weeks (yes vs no) as dependent variable, IG, therapeutic approach (CBT vs PDT) and comorbid SCID-5 personality disorder (yes vs no) as fixed effects, and cooperation centre, supervision group (if possible), and therapist as nested random effects.

The two primary hypotheses are hierarchically ordered and tested one after the other at the two-sided 5% level. Hypothesis II is only tested if hypothesis I could be rejected. If hypothesis I cannot be rejected, hypothesis II is no longer examined confirmatory but exploratory. This procedure ensures a family-wise type I error of 5%.

These analyses will be conducted either in the full analysis set, which is as complete as possible and as close as possible to the intention-to-treat ideal of including all randomised participants,^118^ or in the sample excluding randomised participants who did not receive a single dose (ie, one therapy session). Missing values are implicitly imputed by the chosen model. This allows for a (modified) intention-to-treat analysis, which results in unbiased estimations under the missing-at-random assumption. Missing values for treatment dropout can only be due to both patient and therapist leaving the study.

Sensitivity analysis for primary endpoints: To investigate the robustness of the results of the primary analyses, we will conduct sensitivity analyses with multiple imputation by chained equations as the imputation strategy. Additionally, primary analyses are repeated in the PP sample. Definition PP sample: patients who receive therapy by trained or non-trained and accordingly supervised therapists as intended by their group allocation without protocol deviations. Protocol violations include: (a) patient’s use of non-allowed medications (eg, newly prescribed antidepressant) or not allowed concurrent psychological treatments, (b) less than 12 completed therapy sessions at the end of week 20 (not relevant with respect to the outcome therapy dropout), (c) participants belonging to the IG, but not receiving the intervention in the intended dose, (d) non-compliant completion of assessments (eg, too early or too late). It will be documented (a) whether the protocol violation occurred during or after the study therapy or overlapping and (b) the measurement time point(s) for which the protocol violation is relevant.

Secondary outcomes: Secondary outcomes are examined exploratorily with analogous methods appropriate for the scale level (ie, mixed linear, logistic, ordinal, or Poisson/negative binomial regression). The contrast of the IG versus CG at week 35 of BDI-II changes from baseline of the model of the first primary outcome is used as a result of secondary outcome analysis. Analyses will be conducted up to and including the first follow-up (week 35) and will be repeated at a later time to include the subsequent measurement points (ie, follow-ups 2 and 3).

Mediators: In path models, we test the hypotheses that the patient’s outcome is mediated by the average level of therapeutic alliance across sessions (WAI patient-rated); ratio of unresolved/resolved alliance ruptures (PSQ-Mod patient-rated; categorised in case of low variance); convergence of the patient’s and therapist’s alliance ratings over time (WAI patient-rated/therapist-rated); therapists’ usage of interventions referring to the therapeutic relationship in the here and now; therapists’ usage of nondirective supportive techniques (validation, expressing emotional sympathy, repeating, paraphrasing, summarising; PIL); therapists’ competence in session (empathy); therapists’ adherence to AFT techniques (BIFS-Subscale AFT). We will test for the presence of collider bias in these mediators (eg, using directed acyclic graphs), and, if detected, apply appropriate statistical methods to address it.

Additional analyses: (a) To test whether MAFT-D is equally effective in CBT and PDT, we examine the interaction between IG and therapeutic approach. Prior to this analysis, we examine baseline differences in clinically and theoretically relevant variables (depression severity, chronicity, comorbidity) between therapeutic approaches (CBT/PDT). Variables for which we detect clinically relevant group differences will be added as covariates. Cooperation centre will be included as a random effect. (b) We examine the adherence measure BIFS (adherence with AFT-techniques, observer-rated) as an outcome, with the same approach as in primary analyses (extent of contamination bias). (c) Safety endpoints are determined using frequency tables and, if possible, (mixed) logistic or linear regressions to compare the event frequencies/groups. (d) Subsidiary research questions concern predictors, moderators, and/or mediators (patient-related, therapist-related, patient-therapist match-related and process-related variables) of (a) therapeutic macro and micro outcomes (eg, dropout, alliance), (b) the effectiveness of MAFT-D (eg, presence of a personality or therapeutic orientation as moderators of MAFT-D effectiveness), (c) observer-rated interpersonal therapeutic skills and skills development and (d) the successful resolution of alliance ruptures.

Interim analyses are not planned. For secondary outcomes and analyses, missing values are not imputed and no adjustment for multiple testing is conducted.

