### Sample size calculation, number of study participants

Depressive symptoms: There are no prior studies that closely align with our study in terms of study population, intervention and measurement instruments. In our view, the chosen reference Bambling *et al*^45^) represents the best available compromise, as it examines a population of depressed patients, employs an alliance-focused supervision approach and uses the BDI-II as a measurement instrument. Accordingly, we assume a higher reduction in BDIII after 20 weeks in MAFT-D compared with TAU of 4.0 BDI-II units with a SD of 7.3 BDI-II units. To detect such an effect with a type I error of .05 (two-sided hypothesis), a power of .90, an intracluster correlation coefficient of 0.05, and a cluster size of 2 patients per therapist on average, we need 76 therapists and 152 patients in total (38 therapists and 76 patients per group, PASS 15, tests for two means in a cluster-randomised design).

Treatment dropout: We expect that MAFT-D will reduce the treatment dropout rate after 20 weeks from 30% to 12.5%, corresponding to an OR of 3.0. The expected dropout rate of 30% for TAU is a conservative estimate based on a recent meta-analysis (35% dropout)^7^ and numbers in our own clinic (n=3.357 depressed patients; 33% dropout). Previous studies on different AFT approaches reported a difference in treatment dropout rates of 17.5% or greater (Bambling *et al*: IG1=6.1%, IG2=3%, CG=35%; Constantino *et al*: IG=0%, CG=27.3%; Muran *et al*: IG=20%, CG1=37%, CG2=46%).^45 46 76^ With identical design effects, 58 therapists and 116 patients per group (116 therapists, 232 patients in total) are needed to detect this difference (PASS 15, test for two proportions in a cluster-randomised design). We expect that 3% of the randomised sample are not part of the full analysis set (oriented on numbers from the trial of Schramm *et al*^77^) due to the lack of any data postrandomisation.^78^ Thus, based on the larger sample size required for dropout, a sample of 120 therapists and 240 patients in total has to be enrolled.

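### The primary BDI-II model imposes one baseline slope on every visit, so its claim of no bias under missing-at-random needs a condition; the possible bias at week 20 is small and one model term removes it

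*Protocol article*

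**What the plan says.** Under Statistical analyses, the first primary outcome is change in BDI-II from baseline, analysed in a linear mixed model with repeated measures. The terms are "IG, therapeutic approach (CBT vs PDT), time and comorbid SCID5 personality disorder (yes vs no) as fixed effects", followed by "baseline BDI-II score as covariate, time by IG interaction" and nested random effects. Time by group is the only interaction listed.

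On the visits to be used: "Measurement points up to and including the first follow-up (within the current funding period) will be considered". Table 1 (Measurement time points) schedules the patient BDI-II at "Screening, BA, after the fifth therapy session, Post, FUP 1, 2, 3". The post-baseline records up to the first follow-up are therefore week 20, week 35 and, on a literal reading, the one after session 5.

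The confirmatory estimate is one contrast from this model: "The contrast of the IG after 20 weeks is the result of the primary analysis". Missing values are left to the model, "which results in unbiased estimations under the missing-at-random assumption". The robustness checks include "sensitivity analyses with multiple imputation by chained equations as the imputation strategy".

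**The concern.** A single baseline coefficient says that a patient one point higher at baseline differs in expected change by the same amount at every visit. Change may depend on baseline differently after five sessions than at week 20 or week 35. If so, the common slope is an average over visits and is wrong at week 20.

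With complete data this would not matter, because randomisation balances baseline between the arms. It does not guarantee balance among patients still observed at week 20. If one arm loses more high-baseline patients than the other, the contrast relies on the modelled week-20 slope to make up the difference. Baseline and arm are both observed, so such data are missing at random. This is a case in which the article promises no bias and the listed model need not deliver it.

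The estimate at stake is the confirmatory one, and it also decides whether hypothesis II is tested confirmatorily.

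**Working it through.** **Inputs from the article.** The planning effect and SD are "compared with TAU of 4.0 BDI-II units with a SD of 7.3 BDI-II units". The plan uses two-sided alpha 0.05, power 0.90, ICC 0.05 and two patients per therapist (Sample size calculation). The required analysis sample is 116 patients per group, with 15% loss in BDI-II at post-assessment and no split by arm.

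**Inputs that are assumptions.** Baseline mean 30, SD 8, floor 20 (the entry criterion); residual SD 7.3; within-patient correlation 0.5; missingness logistic in baseline; and the baseline slopes by visit. The article gives none of the slopes and no missingness by arm or by baseline.

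**Step 1: the plan's own figure.** n per arm = 2 × (1.960 + 1.282)² × (7.3/4.0)² = 70. The design effect is 1 + (2 − 1) × 0.05 = 1.05, and 70 × 1.05 = 73.5, or 37 therapists by the normal approximation. With the noncentral t distribution, power is 0.894 at 37 and 0.902 at 38 therapists per arm. The stated 38 therapists and 76 patients per group are reproduced.

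**Step 2: the yardstick.** With 116 × 0.85 = 98.6 observed per arm, SE = 7.3 × √(2 × 1.05 / 98.6) = 1.065.

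**Step 3: the mechanism.** To first order,

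bias at week 20 ≈ (true week-20 slope − fitted common slope) × (mean baseline of observed MAFT-D patients − mean baseline of observed TAU patients).

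The contrast is MAFT-D minus TAU in change, so a negative bias favours MAFT-D. Take slopes −0.2/−0.5/−0.6 at session 5/week 20/week 35, with missingness log-odds per baseline SD of 0.5 in TAU and 0 in MAFT-D.

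- Three visits: the fitted slope is −0.418 and the baseline gap 0.53, so (−0.500 + 0.418) × 0.53 = −0.043. The full fit gives −0.040 − 0.020 = −0.060.
- Weeks 20 and 35 only: the fitted slope is −0.549 and the gap 0.52, so (−0.500 + 0.549) × 0.52 = +0.025. The full fit gives 0.066 − 0.032 = +0.034.

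The full fit is somewhat larger because the random intercept also borrows from the other visits, where the common slope errs in the opposite direction. The sign flips because session 5 makes the common slope flatter than the week-20 slope, whereas week 35 makes it steeper.

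**Step 4: range.** Large-sample fits (N = 200,000, patient random intercept). Entries are the common-slope estimate minus the baseline-by-time estimate, in BDI-II points. Missingness is about 13% to 17% per arm.

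| True slopes (session 5/wk 20/wk 35) | Log-odds per SD, TAU vs MAFT-D | Three visits | Weeks 20 and 35 |
|---|---|---|---|
| −0.5 at all visits | any pattern tried | 0.00 | within 0.01 |
| −0.2/−0.5/−0.6 | 0.5 vs 0.5 | within 0.01 | within 0.01 |
| | 0.5 vs 0 | −0.06 | +0.03 |
| | 0.5 vs −0.5 | −0.10 | +0.06 |
| | 1 vs −1 (extreme) | −0.25 | +0.12 |
| −0.1/−0.6/−0.8 | 0.5 vs 0 | −0.10 | +0.07 |
| | 0.5 vs −0.5 | −0.16 | +0.13 |
| | 1 vs −1 (extreme) | −0.39 | +0.25 |

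With about 21% missing in TAU and 8% in MAFT-D, and the same log-odds of 0.5 in both arms, the bias is 0.03 to 0.10 in size when slopes differ. With equal slopes it stays at 0.00, even at 24% versus 7% missing.

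A separate simulation at trial size (n = 240, 4,000 trials per scenario, three visits) gave −0.06 to −0.33 with the common slope. With baseline by time the bias was within 0.03, and the SE was the same at about 1.06.

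**Step 5: consequence.** At SE 1.065, a bias of 0.10 moves two-sided alpha from 0.050 to 0.051, 0.15 moves it to 0.052, and the extreme 0.39 to 0.065. Power at a true effect of 4.0 is 0.964. It falls to 0.951 if a bias of 0.15 works against the effect.

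**The case against.** The strongest reply is that nothing in the article shows the two conditions to be met.

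- **Slopes.** No baseline slope is given at any visit. A reader might infer that arm-different, baseline-related missingness alone biases the contrast. It does not: with equal slopes the bias is zero. This part of the reply stands.
- **Missingness.** A reader might take the expected therapy dropout of 30% versus 12.5% as the pattern of missing BDI-II data. The article does not support that. Leaving therapy is not the same as missing the assessment, and Methods against bias provides a €150 incentive for a post-assessment after dropout, which works against differential loss. The 15% loss is described as loss of therapists together with their patients, with no link to severity. This also stands.
- **Session 5.** The session-5 BDI-II appears under the subsidiary research questions as a measure of early change, so it may not belong in the primary model. A reader might infer that the bias favours MAFT-D. That holds only if session 5 enters and TAU loses more high-baseline patients. With weeks 20 and 35 alone the bias is smaller and reversed.
- **Multiple imputation.** Chained equations can model each visit separately. In a check on two of the unequal-slope scenarios, imputing with baseline and arm as predictors reduced the bias from −0.29 to 0.00 and from −0.20 to −0.015. But this is a sensitivity analysis; the confirmatory result still comes from the common-slope model.
- **Left to the analysis plan.** A main-effect baseline covariate is a legitimate choice, and details are deferred to an analysis plan not shown. However, the article lists the model terms explicitly and states the missing-at-random property without condition, so this is a stated specification and not an omission.

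**Conclusion.** The point holds as a small, conditional one. As listed, the model fixes one baseline slope across visits, and the statement about missing-at-random is too strong because it also needs a correctly specified mean model.

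Bias at week 20 requires both visit-specific baseline slopes and baseline-related missingness that differs by arm. Both are assumptions. Under them it is roughly 0.04 to 0.2 points (0.2/4.0 = 5% of the planning effect; 0.2/1.065 = 0.19 SE), and about 0.4 points only in extreme scenarios. The direction is not fixed.

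A reader might go further and conclude that the primary analysis is invalid or the sample size inadequate. Neither follows: alpha and power barely move in the plausible range, and the planned sample size is reproduced.

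**What to change.** In the hypothesis I model under Statistical analyses, add a baseline BDI-II by time interaction to the fixed effects. State that it is kept whatever its p value, so that the elimination rule for the time-by-group interaction does not extend to it. Do the same with the relevant baseline score in the analogous repeated-measures models for secondary outcomes. Reword the missing-data sentence to say that estimates are unbiased under missing-at-random given a correctly specified model.

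The cost is one degree of freedom if only weeks 20 and 35 enter, or two if session 5 enters as well. No new data are needed, precision was unchanged in the simulation, and the sample size stays as it is. The change can go into the analysis plan, which is due before database lock.
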